## 4 TRIAL DESIGN

The trial is a phase IV randomised factorial design controlled trial comparing carbamazepine, levetiracetam or active monitoring combined with or without sleep behaviour intervention. We have used a factorial trial design as this approach enables the efficient simultaneous investigation of AED (carbamazepine; levetiracetam; no AED) and sleep behaviour intervention (vs standard care) by including all participants in both analyses. In a factorial trial it is also possible to consider both the separate effects of each intervention and the benefits of receiving both interventions together (for example levetiracetam and sleep intervention).

## **5 TRIAL SETTING, SELECTION OF CENTRES/CLINICIANS**

The CASTLE trial will take place in NHS out-patient paediatric epilepsy and general paediatric clinics in the UK.

### **5.1 Selection of Centres/Clinicians**

Criteria for the selection of centres will be determined by the Trial Management Group (TMG) and will be described in the supplementary document 'Site Suitability Assessment'.

Initiation of centres will be undertaken in compliance with CTRC Standard Operating Procedures (SOPs); centres fulfilling the criteria will be selected to be recruitment centres for the CASTLE trial and will be opened to recruitment upon successful completion of all global (e.g. governance, ethical, and regulatory approvals) and study-specific conditions (e.g. site personnel training requirements) and once all necessary documents have been returned to CTRC as detailed in the trial 'greenlight' checklist.

Participant identification centres (PICs) might also be used to assist with patient recruitment. A centre will be defined as PIC when the hospital does not have enough resources to carry out the trial. PICs will refer patients to participating centres, where consent will be taken.

## 6 TRIAL POPULATION

### 6.1 Inclusion Criteria

Patients with the following characteristics will be eligible for inclusion in the trial:

- a. Children diagnosed with RE (see International League Against Epilepsy Diagnostic Manual at <https://www.epilepsydiagnosis.org/syndrome/ects-overview.html>)
- b. EEG showing focal sharp waves with normal background (see International League Against Epilepsy Diagnostic Manual at <https://www.epilepsydiagnosis.org/syndrome/ects-eeg.html>)
- c. Aged  $\geq 5$  years and  $< 13$  years at the time of randomisation
- d. Currently untreated with antiepileptic drugs
- e. Written informed consent received from person with parental responsibility/legal representative.
- f. Family have an email address and regular internet access (for online sleep intervention)
- g. Parent and child are to have a good understanding of the English language

### 6.2 Exclusion Criteria

Patients with the following characteristics will be excluded from the trial:

- a. Known contraindication to any of the trial drugs
- b. Previously treated for epilepsy with antiepileptic drugs

### 6.3 Sub-study Inclusion Criteria

Parent-child dyads meeting the trial criteria and the following characteristics will be eligible for inclusion in the qualitative sub-study:

- a. Ability of parent and child to speak conversational English.
- b. Additional consent to main trial: Consent of parent to participate and for their child to participate.

### 6.4 Co-enrolment Guidelines

To avoid potentially confounding issues and to minimise the burden on participants, ideally participants should not be recruited into other clinical trials during their participation in CASTLE. Where recruitment into another trial is considered to be appropriate and without having any detrimental effect on the CASTLE trial this must first be discussed with the CTRC who will contact the Chief Investigator ([name]).

## 7 RECRUITMENT AND RANDOMISATION

### 7.1 Participant Identification and Screening

All patients aged  $\geq 5$  and  $< 13$  years with diagnosis of RE previously untreated with AED will be screened at the trial centres to identify potentially eligible participants for the trial. A 'Screening log' will be maintained of all the patients who undergo screening regardless of whether they are assessed as eligible or decide to participate in the trial as this will provide important information for monitoring purposes. Reasons for not being eligible will be recorded. Reasons for declining to participate will be asked routinely but it will be made clear that patients, parents or carers do not have to provide a reason unless they wish to do so.

Potentially eligible patients (i.e. those that meet the eligibility criteria) and those providing consent (person with parental responsibility/legal representative) will be invited to participate in the trial and provided with a patient information sheet and consent (PISC) form. The patient and the person providing consent will be allowed sufficient time to discuss the trial and decide whether to assent/consent to trial entry (see section 7.2 for assent and consent procedures).

### 7.2 Informed Consent

Informed consent is a process initiated prior to an individual agreeing to participate in a trial and continues throughout the individual's participation. Informed consent is required for all patients participating in CTRC coordinated trials. In obtaining and documenting informed consent, the investigator should comply with applicable regulatory requirements and should adhere to Good Clinical Practice (GCP) and to the ethical principles that have their origin in the Declaration of Helsinki.

#### 7.2.1 Consent procedures

Proxy consent from an appropriate adult (a person with parental responsibility for the child or a person acting as the child's Legal Representative) is required to be obtained in CASTLE due to eligible patients being minors in accordance with the Medicines for Human Use (Clinical Trial) Regulations 2004 and amendments.

Proxy consent should be obtained prior to each patient participating in the trial, after a full explanation has been given of the treatment options, including the conventional and generally accepted methods of treatment.

Discussion of objectives, risks and inconveniences of the trial and the conditions under which it is to be conducted are to be provided to minors (to an extent appropriate for each minor's capacity of understanding) and the appropriate adult providing consent on their behalf by a medically qualified doctor with experience in obtaining informed consent in this population. Patient information and consent forms, describing in detail the trial interventions/products, trial procedures and risks will be approved by CASTLE's Research Ethic Committee (REC) and the appropriate adult will be asked to read and review the document.

Upon reviewing the document, a delegated member of the research team will explain the research trial to the minor (to an extent appropriate for each minor's capacity of understanding) and the appropriate adult. This information will emphasise that participation in the trial is voluntary and that the participant may withdraw from the trial at any time and for any reason. All minors and appropriate adults will be given opportunity to ask any questions that may arise and should have the opportunity

to discuss the trial and time to consider the information prior to agreeing to participate. A contact point where further information about the trial may be obtained will be provided.

Minors and the appropriate adults providing consent on their behalf will have as long as they require to consider their decision to join the trial or not and they may join the trial on the same day if that is their wish. The right of the appropriate adult approached for consent (person with parental responsibility / Legal Representative) to refuse consent for the minor to participate in the trial without giving reasons must be respected.

If willing to provide consent, the appropriate adult will then sign and date the informed consent document. Both the person taking consent and the appropriate adult must personally sign and date the form. A copy of the informed consent document will be given to the appropriate adult for their records. The original will be filed in the Investigator Site File (ISF) and a further copy will be retained in the participant's notes. One final copy of the consent form should be sent to the CTRC.

After the patient has entered the trial, the clinician will remain free to give alternative treatment to that specified in the protocol, at any stage, if s/he feels it to be in the best interest of the patient. However, the reason for doing so should be recorded and the patient will remain within the trial for the purpose of follow-up and data analysis. Similarly, the appropriate adult who has provided consent on behalf of the patient remains free to withdraw the patient at any time from the protocol treatment and trial follow-up without giving reasons and without prejudicing the further treatment of the minor.

### **7.2.2 Parental Responsibility; Who is eligible to provide proxy consent?**

Parental consent may be obtained from those with parental responsibility for the child in accordance with the Clinical Trials Regulations (SI 2004/1031 as amended).

### **7.2.3 Assent of minors**

If capable, and under appropriate circumstances, minors of  $\geq 7$  years should be approached to provide assent by a medically qualified doctor with experience with minors. Age-and-stage-of-development-appropriate REC-approved patient information sheet and assent forms, describing (in simplified terms) the details of the trial interventions, trial procedures and risks, are available. The minor should **personally** write their name and date the assent form (or otherwise personally mark the form, as they are able), which is then signed by the appropriate adult providing consent in the minor's behalf and the researcher taking assent.

Assent forms do not substitute the consent form signed by the appropriate adult providing consent on the minor's behalf (see section 7.2.1). Assent should be obtained where appropriate and documented in the patient notes. Minors who are approached for assent must provide this in order to be entered into the trial; the original completed assent form must be retained in the ISF, a copy given to the minor and another copy filed in the patient medical notes and a final copy sent to CTRC. However, the absence of assent does not exclude the patient, provided it has been deemed inappropriate to approach the minor for assent and consent has been obtained from the appropriate adult. Reasons for not approaching a minor for assent must be recorded in the patient medical notes and notified to CTRC.

### **7.2.4 Consent for the qualitative sub-study**

As part of the CASTLE consent process, a delegated member of the centre research team will ask whether appropriate adults providing consent are happy for their contact details to be communicated

to the qualitative study team in order for them to be provided with further information so they may consider participating in the qualitative sub-study. The sub-study will require participation of both the child and the appropriate adult.

Additional consent and assent will be sought for the qualitative sub-study by a delegated member of the qualitative research team. Children with RE will only be invited to interview once a person with parental responsibility for the minor (see section 7.2.2) has consented to participation in the sub-study and has given permission for the minor to be approached for assent. Only minors  $\geq 7$  years that are capable will be asked to assent. Persons with parental responsibility for the minor will consent for theirs and the minor's participation. This component acknowledges that children and parents are experts of their own experience. Consequently, inherent power differences (research-participant, adult-child, parent-child) will be sensitively handled. Materials and documentation will be tailored according to specific developmental abilities and produced in collaboration with the PPI panel.

### **7.2.5 Re-consent of minors who reach 16 years during trial participation**

For the purposes of the trial, a minor is defined as under 16 years. Should a trial participant reach age 16 years during the course of their trial participation, they will be re-consented as an adult.

## **7.3 Where consent to participate in CASTLE is declined**

A delegated member of the centre research team may approach those who have declined to participate in CASTLE to request whether they are happy for their contact details to be communicated to the qualitative sub-study team in order for them to be provided with further information so they may consider participating in the qualitative sub-study.

## **7.4 Enrolment/Baseline**

Once consent has been obtained from the appropriate adult, and assent from the child if appropriate, by the delegated member of the research team the eligibility assessments will be completed, full eligibility confirmed (confirmation must be by a medically qualified doctor) and baseline data will be collected prior to randomisation.

## **7.5 Randomisation Procedures**

Patients **should not** be randomised until:

- a) Written informed consent has been obtained from an appropriate adult and assent if appropriate obtained from the patient;
- b) All eligibility criteria have been fulfilled and full eligibility has been confirmed by a medically qualified doctor and this has been recorded in the patient's medical notes and on the Eligibility case report form (CRF);
- c) The Baseline CRF has been completed.

All participants will be randomised firstly between carbamazepine or levetiracetam or active monitoring in a 1:1:1 ratio, and secondly between PBS or standard care in a 1:1 ratio (see flow diagram, Figure 1). A subset of participants will be purposively selected to wear an actigraphy watch and participate in the actigraphy sleep monitoring component.

If allocated to carbamazepine or levetiracetam, the randomised treatment should ideally begin on the day of randomisation, or within 14 days of randomisation at the latest. If the participant has been selected to wear an actigraph, the treatment should not commence until the actigraph has been worn for the first week (however treatment should still commence within the 14 day window after randomisation). Carbamazepine or levetiracetam treatment should be sourced via usual NHS arrangements (see section 9).

Participants will be randomised using a secure (24-hour) web-based randomisation programme. Allocation sequences will be computer-generated, and concealed from staff recruiting participants to the trial using a secure internet-based system created and maintained by the CTRC. A personal login username and password, provided by the CTRC, will be required to access the randomisation system; designated research staff will be issued with their personal login and password upon completion of training in the use of the system.

When the system requirements (consent and eligibility) are confirmed, the participant intervention allocations and a unique trial number (randomisation number) will be displayed on a secure webpage and an automated email confirmation will be sent to the designated centre personnel and to the trial coordinator (only those recipients who are required to do so will receive information of intervention allocations in the notification email). It is the responsibility of the Principal Investigator (PI) or delegated research staff to inform the pharmacy department at their centre prior to randomisation to ensure there is sufficient supply of the trial treatments.

**Randomisation: web access** <https://ctrc.liv.ac.uk/Randomisation/CASTLE/>  
*If there are any problems with the randomisation systems contact  
 the CTRC on [name] or via email on [[contact]](mailto:[contact])*

(Note that the coordinating CTRC is open from 09:00 – 17:00, Monday – Friday,  
 excluding public holidays)

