#### 3.1.2 The Clinical Trial

This clinical trial is the major component of a programme of work on childhood epilepsy interventions and outcomes. Complementary work packages include the development of a core outcome measure set (Work Package 1); qualitative methods (Work Package 2); and the generation of an online parent-based sleep (PBS) intervention (also referred to as sleep behaviour intervention) for use in the trial (Work Package 3). We will conduct a pragmatic, unblinded, randomised 3x2 factorial trial of anti-epileptic drug (AED) (carbamazepine or levetiracetam or no AED) and sleep behaviour intervention or standard care, to evaluate their comparative effect on seizures, sleep problems, learning and patient-centred outcomes. In addition, engagement via patient and public involvement (PPI) advisory panel(s) will ensure that each stage of the programme is informed by the perspectives of children with rolandic epilepsy (RE) and their parents. An embedded economic evaluation will assess the cost-effectiveness of each intervention, from the perspective of the NHS and PSS.

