### 7.5.2 Contacts Database

The 'contacts database', also called CASTLE Contact Management System, is a secure system hosted by the University of Liverpool designed to be used immediately after randomisation. The system sits between the randomisation system and the online PBS intervention and will collect the required personal and contact details from participants if they have:

- Been allocated to receive the PBS intervention

and/or

- Been selected for actigraphy (and consented to actigraphy)

The required details will be entered in the contacts database by the research team at site. A personal login username and password, provided by the CTRC, will be required to access the contacts database; designated research staff will be issued with their personal login and password upon completion of training in the use of the system. When all fields in the contacts database have been completed and submitted by the research staff at site, an email will be automatically generated and securely sent to:

- the primary carer of the participant, which will include a link to the PBS intervention online and log in details (if the participant is randomised to the PBS arm).

and/or

- the sleep research team at Oxford Brookes University to inform them that a participant has been added so they can view the address and contact the parent/primary carer to arrange the shipment of the actigraphs (if the participant is selected for actigraphy and has consented to this).

The system is password protected and accounts will only be generated for specific members of the sleep research team at Oxford Brookes University and CTRC members that need access to participant's details.

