##### 0 Months (Randomisation) – visit 1:

- Randomisation to Trial Interventions
- Completion of Contact Details Database
- Confirmation of selection for the actigraphy subset

*(At home: actigraphs are sent to the participant's address for those in the subset. Dyads will wear the actigraphs for 1 week)*

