#### **8.2.5.2 Actigraphy**

Although previous studies have demonstrated impaired sleep quantity and quality of parents of children with epilepsy (22), none have employed objective measures to demonstrate whether the impairment is related to a perceived or a measurable deficit in sleep parameters. Actigraphy is a wrist-worn, accelerometer-based method of objective sleep assessment widely used in research and clinical practice and has been used successfully with children, including those with a range of developmental disorders (23, 24).

Up to 15 dyads (child and primary carer) from each of the 6 final trial subgroups will both wear the watches (actigraphs) for 1 week at baseline, 3 and 12 months during the trial. However, only the data from a purposeful sample of 10 dyads from each group will be analysed; this is to account for any drop outs or incomplete data. Actigraphy data will let us look at baseline sleep patterns, the relationship between the primary carer and the child's sleep, and the impact of different treatments during the trial. Summary variables of sleep latency, total sleep time and sleep efficiency will be used for analysis. Along with the actigraphs, parents/primary carers will be asked to complete a sleep log that will capture 'lights out', subjective sleep times, when the watch was put on/off, exceptions circumstances, etc. Participants might also contribute to log completion if they have capacity to do so but parents are intended to be the key recorder. The information recorded in the sleep logs will be used to facilitate subsequent analysis of actigraphy data.

When a new participant is selected for actigraphy, the sleep research team at Oxford Brookes University will be notified via email so they can proceed to:

1. Log in to the contacts database and view the participant's name, address, phone number and email
2. Contact the parent/primary carer to arrange a convenient time for the shipping of the actigraph and answer any questions they might have
3. Ship the actigraphy equipment together with instructions in the use of the watches and its return, as well as the sleep log (paper document) and contact details for troubleshooting any problems. The shipment will ideally occur within 1-2 days after randomisation but it is acknowledged that it might not always be the case and it will depend on the timing of randomisation and the availability of the parent/primary carer to receive the package.

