##### 9.1.1.1 Actigraphy cohort

Baseline actigraphy is defined as the data collected from sleep patterns before the participant starts trial medication. The participants selected to wear an actigraph watch will be asked to wear the watch for one week and start medication and/or sleep intervention (if relevant) immediately after the actigraph has been removed. Actigraphs will be sent directly to the participants' address as soon as possible after randomisation (should be sent ideally within 1-2 days following randomisation). If actigraphs are not received before night 7 post-randomisation then the participants will not be able to wear the actigraphs as it will not allow treatment to commence within the 14 day window.

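### Actigraphy wearers are chosen purposively around the point where allocation is displayed, with quotas filled by allocated group, so the actigraphy comparison of treatments is not protected by randomisation

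*Protocol*

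**What the plan says.** Section 7.5 fixes the method of entry: "A subset of participants will be purposively selected to wear an actigraphy watch and participate in the actigraphy sleep monitoring component". It gives no criteria and does not say who selects.

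Section 8.1.1, under the randomisation part of visit 1, lists randomisation, then the contacts database, then "Confirmation of selection for the actigraphy subset". Under section 7.5, once consent and eligibility are confirmed, "the participant intervention allocations and a unique trial number (randomisation number) will be displayed on a secure webpage". Section 3.1.2 describes the trial as open: "We will conduct a pragmatic, unblinded, randomised 3x2 factorial trial". The contacts database, which takes details of participants selected for actigraphy, is "designed to be used immediately after randomisation" (section 7.5.2).

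Section 8.2.5.2 sets the quota: "Up to 15 dyads (child and primary carer) from each of the 6 final trial subgroups". It gives the effect of the different treatments as one use of the data. Table 1 (section 3.3) lists change in sleep parameters across treatment groups under Other Objectives.

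Section 9.1.1.1 asks wearers to "start medication and/or sleep intervention (if relevant) immediately after the actigraph has been removed". Section 7.5 keeps the 14-day limit on starting a drug, and section 9.1.2 holds the sleep-intervention login until day 12 for wearers.

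**The concern.** A comparison between subsets of randomised groups keeps the protection of randomisation only if entry to the subset cannot depend on allocation. Here entry is by judgement, its confirmation belongs to a step at which the allocation is on screen, and the target number is set for each allocated group.

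There is also a plausible reason for entry to differ. A family allocated a drug or the parent-based sleep intervention (PBS) must wait for the watch to arrive and be worn before starting. A family on active monitoring with standard care has nothing to postpone. Staff or families may therefore weigh selection differently in different groups.

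At stake is the only objective sleep measure in an open trial whose primary sleep outcome, the Children's Sleep Habits Questionnaire (CSHQ), is completed by parents and classed as subjective in section 8.2.5.1. If wearers differ between groups at entry, a difference in actigraphy cannot be attributed to treatment on the strength of the randomisation. More dyads would not cure this.

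**Working it through.** The protocol states no sample size, power or error rate for actigraphy, so there is no figure to reproduce. The check has two parts.

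**1. Does the text separate selection from allocation?**

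- Method: purposive (7.5).
- Point in the visit: confirmation is listed under the randomisation step, not under baseline (8.1.1).
- Knowledge of allocation then: displayed by the system (7.5) in an unblinded trial (3.1.2).
- Quota: up to 15 in each of six allocated groups (8.2.5.2), so 6 × 15 = 90 wearers and 90/330 = 27% of the trial.
- Safeguard: none stated.

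At some point the filling of quotas must use the allocation, and no stated step stops the choice of child from using it too.

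**2. How large could a bias be?**

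This is an illustration, and none of its inputs comes from the protocol. Suppose a fraction *f* of children in every delayed group does not enter because of the delay, and their mean sleep value differs by *d* SD from the rest. Each delayed group's mean then shifts by *f·d*.

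| Allocated group | Postponed for wearers | Shift |
|---|---|---|
| Carbamazepine + PBS | drug and PBS | *f·d* |
| Carbamazepine + standard care | drug | *f·d* |
| Levetiracetam + PBS | drug and PBS | *f·d* |
| Levetiracetam + standard care | drug | *f·d* |
| Active monitoring + PBS | PBS | *f·d* |
| Active monitoring + standard care | nothing | 0 |

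Pooling over the other factor, as a factorial main-effects analysis does:

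- Either drug against active monitoring: *f·d* − (*f·d* + 0)/2 = *f·d*/2.
- PBS against standard care: *f·d* − (*f·d* + *f·d* + 0)/3 = *f·d*/3.

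With *d* = 0.5:

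| *f* | Drug contrast (SD) | PBS contrast (SD) |
|---|---|---|
| 0.10 | 0.025 | 0.017 |
| 0.30 | 0.075 | 0.050 |
| 0.50 | 0.125 | 0.083 |

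For scale, section 8.2.5.2 has 10 dyads per group analysed, giving 20 v 20 for a drug contrast and 30 v 30 for PBS. With unit SD and no baseline adjustment the standard errors are √(2/20) = 0.32 and √(2/30) = 0.26. The largest illustrated biases are thus about 0.4 and 0.3 of a standard error.

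**The case against.** Several points on the other side are sound.

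- **Choice with the allocation in view is inferred.** The schedule speaks of confirming a selection, which allows for earlier nomination, and section 8.1.1 says its lists run in order of priority, so the listed order need not be the order in time. Quotas by group could also be capped by a system without any clinician using the allocation. The inference from an open display, group quotas and a post-randomisation database is strong, but it remains an inference. If nomination comes earlier, the text should say so.
- **Consent may already precede allocation.** Sections 7.5 and 8.1.1 place main-trial consent before randomisation, Table 2 requires it before any procedure, and section 7.5.2 refers to families who have consented to actigraphy. No later actigraphy consent is described, and the consent forms are not to hand. This weakens the idea that families agree or refuse according to allocation. It does not touch selection by staff.
- **The baseline week is untreated.** Section 9.1.1.1 delays treatment for this purpose. Adjusting for baseline actigraphy would deal with much of an entry difference in measured sleep, though not with unmeasured reasons for selection or refusal.
- **The objective is a minor one**, with no power claim and some purely descriptive uses.

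A reader might also infer that the delay itself breaks randomisation. It does not, because it follows from needing an untreated baseline, and drug starts stay within the 14-day limit. Nor is actigraphy the only sleep comparison across drug groups: the CSHQ regression in section 11.5.1 contains a drug factor and uses the randomised groups.

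**Conclusion.** The point holds in limited form. The protocol fixes purposive entry to a subset that it then uses to compare treatments, and states nothing that keeps entry independent of allocation. The actigraphy comparison is therefore not protected by randomisation. Neither primary comparison loses its randomised basis.

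The start delay in five of six groups supplies a plausible reason for differential entry, and no more than that. Direction and size are unknown. The illustrated 0.025 to 0.125 SD (drug) and 0.017 to 0.083 SD (PBS) rest on assumed values of *f* and *d*, on equal deterrence in all delayed groups, and on no baseline adjustment.

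A reader might take the full *f·d*, 0.05 to 0.25 SD, as the bias. That would need a comparator in which no delay deters anyone, whereas only one of the six groups has nothing to postpone. The documents give no ground for assuming that one kind of delay deters and the other does not. Nor do they show that the missing children would sleep worse.

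The later choice of 10 of 15 dyads for analysis is a separate matter. This point would remain if all wearers were analysed.

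**What to change.** In sections 7.5, 8.1.1 and 8.2.5.2, replace purposive selection with a random draw made by the randomisation system, within each allocated group up to the quota, from families whose actigraphy consent was recorded before randomisation. State that the analysis is by randomised group with adjustment for baseline actigraphy. If consent is already taken at baseline, that part only needs saying.

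If purposive choice is kept, either make the selection before allocation or label the between-group actigraphy results as descriptive.

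The cost is small. Section 13.3 already links the contacts database to the randomisation system and has it detect who is selected for actigraphy, so a minor system change is needed. Families could no longer be hand-picked for a spread of characteristics.
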